#### Consumer recruitment

##### Original recruitment protocol

The initial consumer recruitment strategy required local coordinators at each study site to identify potential participants from service administrative and clinical databases using a systematic quota sampling template provided by the study statistician. This method of identifying potentially eligible participants was developed to ensure consumer confidentiality. The site coordinator was then responsible for overseeing the mailing of survey packs to eligible consumers, which contained a 10-page participant information sheet and consent form (PICF), a 2-page questionnaire comprising the QPR and a simple demographic survey (Stream 1 survey), and two color-coded reply paid envelopes. Participants were instructed to return the signed consent form and questionnaire separately in their respective color-coded reply paid envelopes. This strategy was designed to protect participant confidentiality by ensuring that participant data was returned independently of identifying contact information. A unique matching code was printed on each of the forms to allow subsequent data linkage.

The original PICF invited participants to consent to one of four levels of involvement in the study and sign and return the form accordingly. Consent levels were as follows:Level 1 consent refers to a participant consenting to the inclusion of a returned Stream 1 survey into the project.Level 2 consent refers to a participant providing additional permission for the researchers to access and use relevant routinely collected clinical data.Level 3 consent refers to a participant being willing to be contacted for a maximum of two project interviews.Future research consent refers to a participant being willing to be contacted to participate in future research.

However, of the 713 letters mailed out using this initial strategy, only 21 letters (2.9%) were returned over the subsequent 5 weeks.

##### Modified recruitment protocol

Due to this low response rate, the consumer recruitment protocol went through a series of adaptations to facilitate greater engagement and flexibility of recruitment strategies. The primary mode of recruitment through mail out was modified to a) allow mail outs of letters of invitation to complete and return the Stream 1 survey form to all eligible consumers of the participating services from each cluster site; b) replace the 10-page PICF in the survey pack with a simple one-page consent to be contacted for a face-to-face interview form, thus requiring implied consent only for return of the mailed questionnaire and demographic form; and c) provide a $10 shopping voucher for all returned questionnaires where contact details are provided.

A range of secondary recruitment strategies to promote consumer response to the mail outs were added and flexibly employed according to the needs of sites. Strategies include, for example, having researchers, including consumer researchers, present at sites to speak about PULSAR; the use of publicity materials such as advertisements, posters or PULSAR-branded materials; and direct contact with clinicians and consumers at participating sites. Considerable care was taken to ensure, as far as reasonably possible, that recruitment strategies were consistent across time points at participating clusters.

### Allocation

#### Sequence generation

Clusters were randomized to receive the intervention at either step 1 or step 2, see Fig. 1. We used stratified randomization to ensure that cluster types were balanced across arms, see Table 2. The method of sequence generation was by simple randomization using an online Research Randomizer for random number generation. Seven randomization keys were created that corresponded to the seven strata. The randomization was performed offsite by an independent researcher during the third quarter of 2014. Investigators, site coordinators, participants and all others are unable to change the randomization key and intervention allocation given to a site.

### Blinding and procedures to minimize bias

As the intervention involves training, specialist mental health care staff are aware of the intervention condition they are allocated to. Efforts are made to maintain the blindness of research assistants for the onsite recruitment and yearly face-to-face assessments for consumers by withholding information about the allocation of training to clusters and by rotating interviewers across interview and onsite recruitment clusters from T0 and T1. After conducting interviews in streams 2 and 3 of the cRCT, research assistants are asked to classify consumer participants into an intervention condition (PULSAR training provided at their site of service in year 1 or year 2) together with any specific reasons for their response and an estimate of their level of confidence in their judgement to assess whether blindness is preserved.

Procedures adopted to minimize other sources of bias include:Allocation status is recorded in a separate (linked) database from the database containing process and outcome data;Consumer participants are not informed if cluster staff at the service they attend have received the intervention training;The stepped-wedge design can reduce contamination of control clusters as staff in all sites know they will eventually receive the intervention [20, 21];In recruitment, considerable efforts are made to minimize possible sampling bias by ensuring that all eligible consumers are given the opportunity to participate. For example, the multiple levels of involvement (see above *Levels of Consumer Participation*) are designed to offer maximum flexibility for consumers to participate based on possible fluctuations in mental health; andRandomization was performed offsite by an independent statistician according to the procedures described above.

### Data collection

The broad data collection periods are in Fig. 1. As indicated in Tables 1, 3 and 4 and discussed earlier, consumers are offered multiple levels of involvement and can contribute both quantitative data in the cRCT and/or qualitative data in the nested qualitative sub-study. Data collection from staff occurs in the nested qualitative sub-study. The process evaluation sub-study assesses a specific set of existing qualitative, quantitative and documentary data.

### cRCT data collection

In stream 1 of the cRCT, cross-sectional data are collected from mail-outs to consumers at three time points, see Table 1. Stream 1 participants can return a completed QPR/demographic survey anonymously in a provided reply-paid envelope addressed to the researchers if they wish. However, they are invited to provide their contact details on a separate one-page “Participant Contact and Consent Form” if they would like to be mailed a $10 shopping voucher. Participants can additionally indicate on the Participant Contact and Consent Form if they are willing to volunteer for other parts of the PULSAR project, such as a face-to-face interview, by signing a “Consent to Future Contact” section.

In streams 2 and 3 of the cRCT, data are collected in structured face-to-face interviews from a subset of stream 1 consumers who consent to future contact, see Table 1 and earlier section *Levels of consumer participation*. A pool of around 12–14 casual research assistants conduct the face-to-face interviews. Prior to conducting interviews, all research assistants attend a compulsory 2 day training workshop facilitated by senior PULSAR researchers. This training is conducted annually prior to commencement of fieldwork each year to train new staff and maintain the skills of continuing research assistants. Training modules include: research interviewing skills; research interviewing from the consumer perspective; risk assessment, including consumer safety, risk management, and distress management; staff safety, including aggression and risk management; communication skills; research ethics; home visit protocols; and blindness. The first two interviews with consumer participants are supervised by a senior PULSAR researcher, and research assistants are provided with verbal and written feedback at the end of each interview.

Participants who complete a face-to-face interview are required to provide full written informed consent for both the interview and to the researchers accessing routinely collected data using a revised PICF. Study interviews take around 60–90 min. At the end of T0 and T1 interviews, participants are asked whether they would be interested in completing a follow-up interview approximately 12 months later (for stream 3). If participants are willing to be contacted regarding the follow-up interview, they are asked to provide their contact details, give an indication of whether they are likely to relocate in the coming year, and provide the contact details of any friend or family member who might be able to pass on letters from the PULSAR project should they no longer be contactable. If participants are not available for a follow-up interview after re-contacting attempts have been made by the researchers, no additional data will be collected. Given that participants are the recipients of the intervention through services provided by trained specialist mental health care staff, no protocol for discontinued consumer participants is necessary.

All data are recorded on paper forms which are securely stored at the PULSAR administrative site. Procedures to ensure accuracy of data extraction include double entry from selected hard copy forms, range checks and examination of outliers.

For participants who provide Level 2 consent initially, then later all participants who complete a face-to-face interview, routinely collected medical data is extracted from organization-specific medical records, see Table 4. All identifiers are removed from the service record data and replaced with a code, enabling re-identification for the purpose of linkage with the participant’s interview data.

The privacy of all participants is safeguarded in accordance with the National Statement on Ethical Conduct in Human Research [47]. All data is stored on password protected computer systems located within the secure PULSAR administration site. The study data will be stored for a minimum of 7 years, after which time it may be destroyed. Re-identification codes are only accessible to the core research team responsible for data management. It is possible that participant data may be used in a non-identifiable format in future research.

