### REFOCUS

The value and efficacy of system-wide transformation to focus on recovery is yet to be empirically established in Australia. In the UK, a staff training intervention (called REFOCUS) promoting personal recovery and enabling organizational change in specialist mental health services has been developed and trialled [13]. Based on a systematic review and narrative synthesis of existing literature on recovery, the REFOCUS team developed a conceptual framework of personal recovery, which identified five key recovery processes denoted by the acronym “CHIME”: Connectedness, Hope, Identity, Meaning, and Empowerment [14]. This conceptual framework informed the development of a team-based training intervention for community mental health teams in England that was designed to promote recovery through changes in staff and team skills, knowledge, behaviour, values and relationships with consumers [13]. In a large scale cluster randomized controlled trial (cRCT), the outcomes of usual care plus the REFOCUS intervention were compared with usual care only (control) in 27 community mental health teams delivering services to adult patients with psychotic disorders. The primary outcome, personal recovery as assessed using the Questionnaire about the Process of Recovery (QPR), did not differ between the REFOCUS intervention group and controls, although staff-rated functioning and unmet needs did improve in the intervention group [15]. The authors suggest that implementation was the central challenge, and when high-participating teams were compared with low-participating teams, higher participation was associated with higher staff-reported recovery-promotion behaviour and improved consumer-rated QPR. Challenges in implementing the intervention at the team level included variability in staff participation and adherence to recovery-oriented training procedures [16] along with the diluting effects of staff turnover. Participant attrition was higher than anticipated (26% vs 7%) resulting in a reduction in planned statistical power. A further proposed possible reason for the overall lack of difference between the intervention and control group on recovery outcomes is that the 12-month timeframe may have been of insufficient length for the intervention to take effect. On average, patient participants had been using mental health services for more than 15 years, suggesting the possibility of established staff-consumer relationships and entrenched ways of relating to services and problems that may take longer than 1 year to change [17].

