**Fig. 1 Fig1:**
[figure not shown]
PULSAR Specialist Care study design and planned timeline Notes. Indicated at the *bottom* is the study year. The two-step cluster randomise control trial is shown: half the clusters receive the intervention in step 1 and the remaining clusters receive the intervention in step 2. For a summary of the study evaluations see Table 1

**Table 1 Tab1:** Evaluation plan for the PULSAR Specialist Care study

	Sub-study name	Evaluation design	Unit of analysis	Number	Number at each time point	Number in each cluster at each time point	Detectable differences		
							Primary outcome, QPR	Secondary outcome, WEMWBS	Secondary outcome, INSPIRE
cRCT (quantitative data)	Stream 1 (primary analysis)	cross-sectional cRCT (complete step-wedge)	Consumers (mail-out)	756	252 at baseline 252 at step 1 252 at step 2	18	6.34 (medium effect)	NA	NA
	Stream 2	pre- and post-intervention (incomplete step-wedge)	Consumers (interviews)	252 (stream 1 subset)	63 at baseline 126 at step 1 63 at step 2	9	7.68 (medium effect)	4.80 (medium effect)	7.72 (medium effect)
	Stream 3	longitudinal, (same participant, 12-mths apart pre- and post-intervention)	Consumers with diagnosis of psychosis (interviews)	88 (stream 2 subset)	44 at baseline & step 1 44 at step 1 & step 2	6–7	10.94 (medium-large effect)	6.84 (medium-large effect)	11.28 (medium-large effect)
Nested Qualitative study (qualitative data)			Consumers Staff	20–24 20–24	10–12 at step 1 10–12 at step 2	Nested sub-study examining qualitative data collected in study interviews and focus groups			
Nested Process evaluation (both quantitative & qualitative data)			Consumers & staff	The process evaluation assesses a specific set of qualitative, quantitative and documentary data relating to each cluster.					

Notes. The primary analysis examines the primary outcome– the Questionnaire about the Process of Recovery (QPR) - collected in the two-step stepped-wedge cluster randomized controlled trial (cRCT). A subset of consumers in the cRCT participate in study interviews where secondary outcomes measuring well-being, service satisfaction and health economic impact are collected In a yet another subset in the cRCT, longitudinal data are collected via interviews that are 12 months apart from consumers with a diagnosis of a psychotic disorder. Qualitative and process evaluation sub-studies are nested within the overarching cRCT and include information from consumers and staff.

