### Sample size

The primary analysis examines QPR data from consumers in the cRCT (stream 1) and requires a total sample size of 756 consumers from 14 clusters over 3 years (see Table 1). This will be sufficient to detect a medium effect size representing a change in QPR score by 6.34, see Table 1. Secondary analyses that examine data from a subset of stream 1 consumers who participate in stream 2 of the cRCT, requires a total sample size of 252 consumers over the study period. This will be sufficient to detect medium effect sizes in the QPR and two secondary outcome measures (WEMWBS and INSPIRE), see Table 1. Additional secondary analyses to examine longitudinal data from a subset of stream 2 consumers who participate in stream 3 of the cRCT, requires a total sample size of 88 consumers over the study period. This will be sufficient to detect medium-large effect sizes in the QPR and WEMWBS and INSPIRE, see Table 1.

Sample size calculations were based on 14 clusters; intracluster correlation coefficient (ICC) of 0.05; significance level set at 0.05; power of 0.80; and available published [34, 36, 45] and unpublished (INSPIRE) data about distribution properties. All sample size calculations indicate the minimum number of participants we aim to recruit and were done using Stata statistical software *stepped-wedge* [46] Version 11, StataCorp. 2009.

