#### Sensitivity analyses

A missing data analysis will investigate any patterns of missingness. For each primary and secondary outcome component with missing data, multiple imputation using multivariate regression with factors of age, gender, time, and intervention status will produce 100 estimates. Sensitivity analyses will be performed using this multiple imputation to account for missing data and then re-running the analyses. Sensitivity analyses will also include the intervention dosage variable described earlier.

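### Stream 3's detectable differences carry no attrition allowance if 88 means starters, and the listed imputation factors omit the person's own first score

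*Protocol article*

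**What the plan says.** Table 1 (Overall design) describes stream 3 as the same participants interviewed 12 months apart: 88 consumers with psychosis, listed as "44 at baseline & step 1 44 at step 1 & step 2", with 6–7 per cluster at each time point. The detectable differences are 10.94 (QPR), 6.84 (WEMWBS) and 11.28 (INSPIRE).

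The Sample size section gives 14 clusters, an ICC of 0.05, a significance level of 0.05 and power of 0.80. It names no attrition rate and adds: "All sample size calculations indicate the minimum number of participants we aim to recruit".

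The Background section on REFOCUS, the trial that PULSAR adapts, reports: "Participant attrition was higher than anticipated (26% vs 7%) resulting in a reduction in planned statistical power".

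Under cRCT data collection, participants who cannot be reached for the second interview are handled in one clause: "no additional data will be collected".

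The Main analysis plan specifies a linear mixed model with intervention status and time as fixed effects and with clusters and consumers as random effects. The Sensitivity analyses section provides for "multiple imputation using multivariate regression with factors of age, gender, time, and intervention status", applied to each primary and secondary outcome component with missing data, after which the analyses are re-run.

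**The concern.** Two things do not fit together.

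First, the protocol knows that its model trial lost 26% of participants and lost power as a result. Its own longitudinal stream nevertheless states detectable differences that need nearly all of the 88 to complete both interviews. Table 1 reads as if 88 were completed pairs, while the Sample size section reads as if 88 were the number to recruit. If it is the number to recruit, the stated precision is not delivered at the attrition the protocol cites.

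Second, in a paired design the first-interview score is the obvious predictor of the missing second score. The imputation factors are named, and this one is not among them. If the imputation is applied to missed second interviews, each lost person receives the average of the completers in the same period and intervention status, adjusted only for age and gender. If people with low first scores are more likely to be lost, that looks like improvement after training. The sensitivity analysis would then rest on a stronger missing-data assumption than the mixed model it is meant to check.

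**Working it through.** **Inputs.** From the protocol: 14 clusters (7 per sequence), ICC 0.05, power 0.80, alpha 0.05 (taken as two-sided), 44 people per sequence, 26% attrition. Not given: the SD of the QPR, the within-person correlation, and how loss relates to the first score.

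**SD.** A stepped-wedge calculation with fixed period effects, a cluster random effect and 18 per cluster per period gives a stream 1 detectable difference of 0.396 SD. Table 1 states 6.34, so SD = 6.34/0.396 = 16.0. The same SD returns the stream 2 figure: 2.802 × 16 × √(2/126 × (1 + 17 × 0.05)) = 7.68.

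**The stated stream 3 figure.** Year-1 clusters contribute T0 and T1, and year-2 clusters contribute T1 and T2. With free period effects, T0 and T2 are each seen in one sequence only. With complete pairs the effect therefore rests on T1: second interviews in year-1 clusters against first interviews in year-2 clusters.

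Detectable difference = 2.802 × 16 × √(DE₁/n₁ + DE₂/n₂), with DE = 1 + (n/7 − 1) × 0.05.

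- 42 and 42 (6 per cluster): 2.802 × 16 × √(2 × 1.25/42) = **10.94**, as stated.
- 44 and 44 (6.29 per cluster): 10.75, with power 81.4% at 10.94.

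So 10.94 corresponds to 84 pairs. The slack against 88 is 4 people, or 4.5%. It looks like 44/7 rounded down to 6, not a chosen allowance.

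**If 88 start and 26% miss the second interview.** Second interviews per sequence: 44 × 0.74 = 32.56. First interviews stay at 44.

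- Second-interview term: (1 + (4.651 − 1) × 0.05)/32.56 = 0.03632.
- First-interview term: (1 + (6.286 − 1) × 0.05)/44 = 0.02873.
- With no within-person correlation: 2.802 × 16 × √0.06505 = 11.43. Power at 10.94 is Φ(10.94/4.081 − 1.96) = 76%.

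With a within-person correlation (after the cluster effect), the mixed model recovers part of the loss from the first scores. The full generalised least squares calculation gives:

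| Analysis | Within-person correlation | Detectable QPR difference | Power at 10.94 |
|---|---|---|---|
| Mixed model, first interviews kept | 0 | 11.43 | 76% |
| Mixed model, first interviews kept | 0.4 | 11.33 | 77% |
| Mixed model, first interviews kept | 0.5 | 11.27 | 78% |
| Mixed model, first interviews kept | 0.7 | 11.10 | 79% |
| Complete pairs only (about 65) | any | 12.08 | 72% |

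Scaled in proportion, the mixed model gives about 6.9 to 7.1 for WEMWBS and 11.4 to 11.8 for INSPIRE. The complete-pairs analysis gives about 7.6 and 12.5.

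**Imputation.** Suppose there is no true change, 26% are lost, and the log-odds of loss rise linearly as the first score falls. The first-interview mean uses everyone, while the imputed second-interview mean equals the completers' mean. The spurious gain is therefore SD × r × (mean standardised first score of those retained), where r is the pre-post correlation.

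| Odds of loss per SD lower first score | Mean standardised first score, retained | Gain at r = 0.4 | Gain at r = 0.7 |
|---|---|---|---|
| 1.35 | 0.077 | 0.5 | 0.9 |
| 2.2 | 0.184 | 1.2 | 2.1 |

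Under this mechanism loss depends only on the observed first score. A mixed model with a consumer random effect takes that into account, but an imputation without the first score does not.

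**The case against.** The strongest reply is that Table 1 most naturally means completed pairs: it lists the same 44 people at both time points. On that reading 10.94 stands. The Sample size section also calls its numbers minima, so more people may be interviewed than the table shows. This has force, and it is why the first repair is a clarification. It does not remove the ambiguity, because the same sentence speaks of numbers to recruit and no attrition rate appears anywhere in the calculation.

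On imputation, the sentence covers all streams and does not say that an unattended second interview will be imputed. Multivariate regression could impute several outcomes jointly, and further detail may sit in an analysis plan that is not shown. An analysis of missingness patterns is also planned. All of this is fair, so the point is conditional. But the article names the factors, and the one that matters most in a paired design is not among them.

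A reader might go further in four ways that the documents do not support:

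- **Lost participants contribute nothing.** The quoted clause concerns data after re-contact fails. The first interview and the prior year's records are kept.
- **Power falls to 72%.** That requires discarding first interviews that the planned mixed model uses.
- **The 63 pre-training stream 2 interviews per sequence cannot supply 44 pairs.** This treats a recruitment minimum as a cap, and the share who are eligible and willing is not given.
- **Later service records should be extracted for those lost.** It is not established that consent covers that year, and HoNoS is not held in Mind Australia or Ermha files.

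**Conclusion.** The point holds in a limited form. The stream 3 detectable differences correspond to about 84 complete pairs of 88 and include no planned attrition allowance. If 88 are starters and 26% miss the second interview, the planned mixed model detects about 11.1 to 11.4 on the QPR in place of 10.94, with 76 to 79% power at the stated difference. At the 7% that the model trial had anticipated, the mixed model still has about 80% power.

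The imputation issue is the more useful of the two. If applied to missed second interviews with only the listed factors, it can produce a spurious pre-post gain of about 0.5 to 2.1 QPR points when the true change is zero.

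These figures rest on an inferred SD of 16 (it reproduces all three QPR figures in Table 1), on within-person correlations of 0 to 0.7 for power and 0.4 to 0.7 for the imputation, and on assumed odds of loss of 1.35 to 2.2 per SD lower first score. The documents give neither the correlations nor the odds. Stream 3 is an additional secondary analysis, and the cross-sectional primary analysis in stream 1 is not touched.

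**What to change.** 1. Add the first-interview value of the same outcome to the imputation model used for stream 3. The value is already collected, so this costs one more variable.
2. State whether 88 means starters or completed pairs.
   - If starters, restate the stream 3 detectable differences under a stated attrition rate and for the mixed model actually planned. At 26% the QPR figure is about 11.1 to 11.4, depending on the within-person correlation, which should also be stated. The 12.1 / 7.6 / 12.5 set should be used only if the analysis is restricted to complete pairs.
   - If completed pairs, the figures in Table 1 stand. The Sample size text should say so and give the number who must start; at 26% loss, 88/0.74 is about 119.

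The cost is a few sentences and, under the first reading, slightly less favourable stated figures. No change to the design is needed.
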